“Iteration”, according to Rowe, Wright and Bolger [10], refers to presenting participants with a questionnaire comprised of multiple rounds and facilitating participants to change how they answer a question. Although the Real-Time Delphi is essentially round-less, it can incorporate iteration by encouraging participants to re-visit and re-answer questions based on changing feedback. This feedback differs from the definition of “Controlled feedback” which Rowe, Wright and Bolger [10] suggest should be given between rounds. Instead, in the Real-Time Delphi, this feedback, such as how the participant answered the question and how other participants, as a group responded to the question, is provided once the participant has submitted their answer. “Statistical group response” refers to the feedback that is provided to the participants. Instead of the feedback being reflective of all participants who have taken part in the survey after each round, the feedback in the Real-Time Delphi is reflective of the participants who have taken part up to that point in the survey. This is why participants are encouraged to re-visit and re-respond to questions if they wish, to get a reflection of the views of participants at different time points and to capture any changes in consensus. Whilst in a Real-Time Delphi, feedback is not “controlled” by limiting feedback only at the end of distinct rounds, it can be argued that the Real-Time Delphi approach still largely incorporates the key features of the Delphi procedure.

Despite claims that a Real-Time Delphi will improve efficiency of the survey process by removing the strict rounds and the time it takes for participants to complete the survey [6, 8], there is no strong evidence on how it compares to the Multi-Round Delphi.

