#### Real-Time Delphi method

The Real-Time Delphi survey will contain outcomes identified from a systematic review of (1) randomised trials and (2) systematic reviews of randomised trials, of interventions for the treatment of neonatal encephalopathy. In addition, outcomes identified as important to parents/caregivers of infants who have been diagnosed with and received treatment for neonatal encephalopathy identified through one-to-one interviews will be included. The survey will also include a short questionnaire seeking participant demographic information.

Participants will be asked to rate the importance of each outcome for inclusion in the COS using a 9-point Likert scale used commonly in the Delphi method for COS development [4]. For each outcome, the participant will be able to view how they rated each outcome, the overall rating results for each outcome and the results for each outcome from each stakeholder group, in real-time. This information will be displayed as feedback immediately after a participant rates an outcome for the first time. With this feedback, participants will be able to modify their answer or keep it the same before moving on to the next outcome. Participants will be encouraged to suggest additional outcomes that they feel are omitted from the list of outcomes presented in the survey. Additional outcomes will be reviewed within 2 days by a representative subgroup from the COHESION Steering Group (i.e. parents/caregivers, healthcare providers and researchers) and included in the Real-Time Delphi survey, if not already captured in the outcomes list. As the degree of consensus changes, depending on how participants rate an outcome, we will encourage participants to re-visit the survey and review their answers based on the degree of consensus. If a participant scores 6 or more points different on the 9-point scale from that given by overall group consensus score (e.g. if the overall group consensus is that an outcome is extremely important and ranks 9 on the Likert scale, and the participant rates it extremely unimportant, as 1 on the Likert scale and vice versa), they will be given the option to comment on the reasoning behind the rating they have given. Participants can save and re-visit the survey to complete the questions and/or modify their answers.

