#### Secondary outcomes

We will compare the outcomes that are prioritised (based on Table 1), from each survey arm, against the final COS.

Additional secondary outcomes are informed by previous comparison of Multi-Round Delphi method and the Real-Time Delphi method by Gnatzy et al. [8]:
2.*Feedback effect*

We will calculate the “feedback effect”, which will inform if, and how, the feedback provided to participants resulted in them amending how they rated an outcome. In the Multi-Round Delphi, participants will be given time (1 week) to process the feedback before the next round, where they can re-rate the outcomes. In contrast, in the Real-Time Delphi, participants will be provided with feedback in real-time. They will be given the option to change their rating or keep their answer the same before moving on to the next outcome. To estimate the feedback effect, we will test the null hypothesis:H0_1_: There is no difference in how participants react to feedback in both survey arms

We will use the following model to estimate this effect:
$$ {cor}_{kl}={b}_o+{b}_1\ast {dev}_{kl}+{b}_2\ast \gamma k+{b}_3\ast \left(\gamma k\ast {dev}_{kl}\right) $$*k*: participants of both Multi-Round and RT Delphi surveys*l*_s_: the projection dependent on *s* which indicates whether the projections (outcome rating) are from the Real-Time (*s* = 1) or Multi-Round (*s* = 2) Delphi study.cor_*kl*_ will indicate how strongly the *expected-probability (EP) values* were corrected after feedback was given.Dev_*kl*_: how strongly a stakeholder deviated from the final expected-probability value.γk∈{0, 1}: an indicator variable which takes on the value 1 if the expert *k* belongs to the Real-Time and 0 if an expert belongs to the Multi-Round Delphi study.*b*_1_: slope coefficient*b*_2_: indictor variable*b*_3_: interaction term3.*Initial condition effect*

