To ensure that the first participant of the Real-Time Delphi survey is provided with feedback, a representative group of stakeholders (five of each parents/carers, healthcare providers and researchers) will vote on the importance of the outcomes (i.e. “initial conditions”) before the survey goes live to the public. These “initial conditions” may have an impact on how outcomes are rated subsequently during the survey process; we call this the “initial condition” effect. In addition, it may be suggested that participants engaging later in the survey have a greater level of feedback than early participants. This might influence how outcomes are re-rated. To identify if the initial conditions effect the final list of outcomes, we will test the hypothesis:H0_2_: There is no effect of the initial conditions on the outcomes that emerge as important at the end of the Delphi survey.

We will conduct a regression analysis with initial conditions and final results. The initial conditions will be the independent variable and final results will be the dependent variable. Furthermore, we will test whether the initial conditions cause participants to change their rating on outcomes compared to late participants. For this, we will use a linear regression model.
$$ {\mathrm{cor}}_{ij}={\beta}_0+{\beta}_1\ast {\mathrm{dev}}_{ij}+\beta 2\ast {\upvarphi}_i+{\beta}_3\ast \left({\upvarphi}_i\ast {\mathrm{dev}}_{ij}\right) $$*i*: participants in the Real-Time Delphi survey*j*: the projection (outcome rating)cor_*ij*_: how strongly the stakeholder’s *EP* assessment was altered after proving feedbackdev_*ij*_: how strongly a stakeholder differed from their *EP* valueφ_i_ ∈{0,1} represents an indicator variable where the value is 1 if the stakeholder *i* is an early participant (week 1) or 0 if the stakeholder is a late participant (week 4).

This model was developed by Gnatzy et al. [8] predicts how the deviation from average EP impacts corrections whilst accounting for possible differences between early and late respondents.
4.*Iteration effect*

In a Multi-Round Delphi survey, participants can only re-rate the outcomes in the second and third rounds. However, in the Real-Time Delphi, participants have the opportunity to re-visit the survey and re-rate the outcomes as many time as they wish. This difference in the iteration (“iteration effect”) could impact the consensus process.

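### The feedback model measures deviation from a final value that participants had not seen when they re-rated, so b1 and b3 are biased if the group rating moves between display and close

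*Protocol article*

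**What the plan says.** Under Secondary outcomes (Feedback effect), the Protocol article states the null hypothesis as "There is no difference in how participants react to feedback in both survey arms". It is tested by regressing cor on dev, an arm indicator (1 = Real-Time) and their product, with coefficients b1, b2 and b3. The response cor is how strongly the expected-probability (EP) values "were corrected after feedback was given". The regressor dev is "how strongly a stakeholder deviated from the final expected-probability value".

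On what participants actually see:
- Real-Time: Background and rationale says "the feedback in the Real-Time Delphi is reflective of the participants who have taken part up to that point in the survey". The Real-Time Delphi method section adds that this appears directly after the first rating of an outcome.
- Multi-Round: the Second round section presents the round-one distribution by stakeholder group and the overall score. The Feedback effect text adds "In the Multi-Round Delphi, participants will be given time (1 week) to process the feedback before the next round".

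Under Initial condition effect, a model of the same form is used for early versus late Real-Time participants. Its dev is listed as "how strongly a stakeholder differed from their" EP value, but the paragraph below the equation describes the regressor as deviation from the average EP.

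Participants are asked to "rate the importance of each outcome for inclusion in the COS using a 9-point Likert scale". EP is spelled out under Abbreviations but given no formula. The only link to the data is the index that "indicates whether the projections (outcome rating) are from the Real-Time" or the Multi-Round study.

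**The concern.** A test of reaction to feedback needs a regressor that measures the gap between a participant's rating and the feedback that participant received. The final value is something else. It exists only once the survey has closed, and it is built partly from the corrections it is meant to explain. The distance between displayed and final value can also differ by arm, because one arm sees a running result and the other a previous-round result. The protocol itself expects the degree of consensus to change while the Real-Time survey is open.

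At stake is the reading of b3. If it can differ from zero when both arms react identically, rejecting the null hypothesis cannot be attributed to different reactions. In addition, an analyst coding the two models has three reference values for dev (final, own, average) and no stated scale for EP, and would have to choose.

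**Working it through.** **Plan's own figure.** The protocol gives no effect size, SD or power for this model. Its only relevant number is the sample size: 30 per stakeholder group x 3 groups x 2 arms = 180, or 90 per arm, which reproduces.

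**Inputs.** From the protocol: 90 per arm, and 15 seed voters (5 from each of 3 groups) before the Real-Time survey opens. Assumed, because the protocol gives none: rating SD 2, 60 outcomes, true correction between 0 and 0.6 of the gap shown, and the drift and seed offsets below.

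**Simulation.** The model cor = b0 + b1 dev + b2 g + b3 (g x dev) was fitted by least squares, 200 runs per scenario. Multi-Round has one re-rating after the round-one mean is shown (third round omitted). Real-Time is sequential with a running mean that starts from the seed votes. Drift means that Multi-Round ratings shift between rounds, by outcome, for reasons other than feedback. Reaction is equal in both arms except in the last row.

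| Scenario | b1, final | b3, final | b1, displayed | b3, displayed |
|---|---|---|---|---|
| Stable, true 0 | 0.001 | 0.000 | 0.000 | 0.000 |
| Stable, true 0.3 | 0.300 | 0.003 | 0.300 | 0.000 |
| Stable, true 0.6 | 0.600 | 0.008 | 0.599 | 0.001 |
| Seed votes offset by SD 1, true 0.6 | 0.600 | 0.020 | 0.600 | 0.000 |
| Seed votes offset by SD 2, true 0.6 | 0.601 | 0.053 | 0.600 | -0.001 |
| Multi-Round drift SD 1, true 0.3 | 0.441 | -0.138 | 0.300 | -0.001 |
| Multi-Round drift SD 1, true 0 | 0.201 | -0.201 | 0.000 | 0.000 |
| Stable, true 0.3 versus 0.5 | 0.301 | 0.206 | 0.300 | 0.200 |

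**Check by hand.** Let s be the rating SD within an outcome, d the drift SD and c the true correction. With dev taken from the final Multi-Round value, drift enters both cor and dev, so b1 = (c s² + d²) / (s² + d²). The Real-Time slope stays near c, so b3 is about c - b1. With s = 2:
- d = 0: b1 = c and b3 = 0.
- d = 0.5, c = 0: b1 = 0.25/4.25 = 0.059 and b3 = -0.059.
- d = 0.5, c = 0.3: b1 = (1.2 + 0.25)/4.25 = 0.341 and b3 = -0.041.
- d = 1, c = 0: b1 = 1/5 = 0.20 and b3 = -0.20.
- d = 1, c = 0.3: b1 = (1.2 + 1)/5 = 0.44 and b3 = -0.14.

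The last two agree with the simulation.

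**Separate artefact.** cor and dev share the prior rating. With no reaction and retest correlation rho, the slope in an arm is 1 - rho. Under assumed correlations (Multi-Round / Real-Time):
- 0.70 / 0.95: b3 = 0.05 - 0.30 = -0.25.
- 0.80 / 0.95: b3 = 0.05 - 0.20 = -0.15.
- 0.60 / 0.90: b3 = 0.10 - 0.40 = -0.30.

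Simulation with 80 per arm gives -0.256, -0.153 and -0.304 from the final value, and -0.253, -0.151 and -0.302 from the displayed value. The choice of reference makes almost no difference here.

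**The case against.** The strongest reply is that the final value is usually near the one displayed. With stable ratings the bias is negligible, and the 15 seed votes limit how far early Real-Time feedback can stray: even an offset of SD 2 points moves b3 only to 0.053. A material bias needs drift unrelated to feedback, for which the protocol supports no figure. This stands. A reader might infer that b1 and b3 do not measure reaction to feedback at all; the documents do not support that.

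A reader might also infer that the survey fails to collect what the model needs. It does not follow. The protocol glosses the projection as the outcome rating, so EP can be read as the 1-9 rating; the fault is an undefined label. Likewise, a participant's deviation from the own EP value would literally be zero, but the next paragraph speaks of the average, so loose wording is the fairer reading. The definitions still need aligning.

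A third tempting inference is that the -0.15 to -0.30 from unequal retest reliability results from using the final value. It does not, and redefining dev leaves it in place. The assumed correlations are also open to doubt. Multi-Round participants re-score with their own round-one score in view, Real-Time participants may return later, and the different interval is part of the formats being compared.

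The model's coding might be left to an analysis plan. But the protocol writes out the equation and defines its terms, and the stated definition does not match the stated hypothesis.

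**Conclusion.** The concern holds in a limited form. The regressor dev is defined against a value not shown at re-rating, which does not match a hypothesis about reaction to feedback. The resulting bias in b3 ranges from about 0.003 with stable ratings (true correction 0.3) to about -0.20 with an assumed Multi-Round drift of SD 1 point per outcome and no reaction in either arm. The latter is as large as the genuine arm difference of 0.20 in the simulation. Taking dev from the displayed score brings b3 to within 0.001 of zero in every equal-reaction scenario with the retest artefact absent. These sizes rest on the assumed rating SD, number of outcomes, correction strength, seed offset and drift.

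The inconsistent references for dev in the initial-condition model and the missing definition of EP on the 1-9 scale are lesser faults of wording. Retest reliability is a separate caution on interpreting b3. The primary comparison of outcome lists under Table 1 does not use this model and is unaffected.

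**What to change.** - Define EP as the 1-9 rating wherever it is used under Secondary outcomes: the feedback, initial-condition and iteration analyses.
- In both regression models, define dev as the group score displayed to that participant for that outcome just before the re-rating, minus the participant's own prior rating. Define cor as the next rating minus that same prior rating, with a kept rating counted as 0.
- Log the displayed score with each rating, or rebuild it from time stamps.
- State that cor and dev share the prior rating, so that unequal retest reliability between arms can by itself make b3 non-zero. Add a sensitivity analysis using Real-Time re-ratings made at later visits.

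The cost is wording plus one exported or reconstructed field. Trial status says recruitment had not begun, so logging can still be arranged. The downside is that results are no longer comparable term for term with the cited earlier comparison of the two Delphi formats.

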The order in which outcomes will be presented to participants will be randomised within their outcome domains, as Brookes et al. [12] have shown that question order may influence the level of response. In addition, a lay-explanation of outcomes and terminology used in the Delphi survey will be provided as this has been shown to affect the retention of stakeholders positively in a Delphi survey [5].

To avoid a small group of initial participants having a significant influence on the consensus levels and thereby potentially influencing subsequent participants to answer based on those consensus levels, a representative group of stakeholders (5 of each parent/caregivers, healthcare providers and researchers) will vote on the importance of the outcomes before the survey goes live to participants. In this way, consensus information will be available to the first online participant in the same way it will be available for subsequent participants. The timing and frequency of email reminders will be decided by the COHESION Steering Group based on temporal responses.

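### The early/late model for the initial condition effect has no seed-vote term and so cannot show that the seed votes changed ratings; the companion regression that does use the seed votes needs adjustment for first ratings

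*Protocol article*

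**What the plan says.** The Real-Time Delphi method section has a small stakeholder group that "will vote on the importance of the outcomes before the survey goes live to participants", so that the first entrant already sees feedback. Secondary outcomes, item 3, gives its size, "five of each parents/carers, healthcare providers and researchers", which makes 15 voters, and calls their votes the initial conditions. H0_2 states that these have no effect on which outcomes emerge as important.

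Two analyses follow.

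- **First regression.** Final results are regressed on the initial conditions. No other covariate is named.
- **Second model.** It is introduced with the words "we will test whether the initial conditions cause participants to change their rating on outcomes compared to late participants" and printed as cor = β0 + β1·dev + β2·φ + β3·(φ·dev), for Real-Time participants only. φ is 1 for week 1 and 0 for week 4; weeks 2 and 3 have no code. The closing comment says that it "predicts how the deviation from average EP impacts corrections whilst accounting for possible differences between early and late respondents".

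The reference point for dev is not consistent. In this model dev is "how strongly a stakeholder differed from their" EP value. The closing comment speaks of the average EP. The sister model for the feedback effect uses "how strongly a stakeholder deviated from the final expected-probability value".

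**The concern.** The sentence that introduces the second model promises a causal statement about the seed votes, but the equation compares early with late entrants. All Real-Time participants receive seeded feedback, so there is no unexposed group, and φ is at most a rough stand-in for how much of the display the seeds make up. The same section names a rival explanation for any early/late difference, that "participants engaging later in the survey have a greater level of feedback than early participants". People who enter in week 1 may also differ in kind from those who enter in week 4, and they have longer to return and revise.

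H0_2 is the protocol's check on whether seeding altered the Real-Time list. A null result could be taken as reassurance when seeds had moved ratings. A positive result could be blamed on the seeds when it only reflects who enters early. In one set of simulations (set B below), seeds that differed from the panel by about 1 point shifted final means by 0.11-0.24 points and moved about 2-5 of 50 outcomes across the 70% cut-off.

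**Working it through.** **1. The plan's own figure.** 3 groups × 30 = 90 per arm, and × 2 arms = 180, as stated under Sample size. The article gives no alpha, power, effect size, SD or number of outcomes for H0_2, so every input below beyond 90 participants and 15 seed voters is an assumption.

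**2. What the printed model can see.** Let y be a participant's first rating, D the average displayed, F the final average, and w the fraction by which the participant moves towards D. Then cor = w·(D − y).

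- *dev taken from the display, D − y:* cor = w·dev. If w is the same for early and late entrants, β2 = β3 = 0 however far the seeds pulled D.
- *dev taken from the final value, F − y:* cor = w·dev + w·(D − F). The second part differs between early and late entrants if the seeds lean one way, so φ can pick it up.

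Size of that second case: assume all 15 seed votes stay in the display, 30 early entrants, 20 late entrants (the last 20 of 90) and w = 0.4. The seed share seen by an entrant with n predecessors is 15/(15 + n). It averages 0.56 for n = 0 to 29 and 0.16 for n = 70 to 89. A uniform one-point lean then gives β2 ≈ 0.4 × (0.56 − 0.16) = 0.16; simulation gave 0.15.

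**3. Simulated rejection rates for the second model** (nominal 5%, errors clustered by participant).

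- Set A: 600 runs per scenario, 30-60 outcomes, 30 early and 20 late, mean w 0.4 varying between people, joint test of β2 and β3.
- Set B: 1,000 runs, 50 outcomes, within-outcome SD about 1.6, even entry over 4 weeks, fixed w of 0.3 or 0.5, test of β3 unless stated.

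| Scenario | Set A | Set B |
|---|---|---|
| Influential seeds, dev from display | 5-11% (6-7% with no seeds) | 5-7% |
| Seeds leaning both ways, dev from final | 15-26% (25-34% with no seeds) | β3: 5-11% (both seed patterns) |
| Seeds leaning one way, dev from final | 27-41% at 0.5 points; 67-79% at 1; 99-100% at 2 | joint test: 95-99% at 1 point, but 62% with no seeds |
| No seeds, early entrants react more | 38-69% (w 0.5 v 0.4); 94-99% (0.6 v 0.4) | 93% (0.35 v 0.30); 100% (0.40 v 0.30), dev from display |

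A further set of runs gave 8-10% with influential seeds (dev from display) and 77-95% with no seeds and w 0.5 v 0.4. The spread in the last row partly reflects whether w varies between people.

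With dev from the final value, the joint test rejects in 25-34% of set A runs with no seeds and no early/late difference in w. A rejection there is therefore not evidence about seeds even before confounding is considered.

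**4. The first regression as printed.** Seeds and panel both rate outcome j around its true importance. With no influence at all, the expected slope of the panel mean on the seed mean is about τ²/(τ² + σ²/15), where τ is the SD of true means across outcomes and σ the SD within an outcome. With σ = 1.6, σ²/15 = 2.56/15 = 0.171.

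- τ = 0.5: 0.25/0.421 = 0.59
- τ = 1: 1/1.171 = 0.85

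In simulation with no seeds shown, the unadjusted regression rejected in 77-100% of runs in one check and 98-100% in another.

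**5. The first regression, adjusted for participants' mean first rating.** It rejected in 82-100% of set A runs with seeds shown and 4-7% without. In the further runs it rejected in 99.7-100% and 4-6%.

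**The case against.** The strongest reply is that the early/late model is only an addition. H0_2 already has a regression that uses the seed votes directly, nothing says that β3 decides the hypothesis, and the section gives the early/late model a legitimate purpose of its own: to see whether early and late respondents behave differently. The model is also taken from a cited study, and an analysis plan may fix the definition of dev and the coefficient tested.

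Much of this stands. A reader might infer that no H0_2 analysis uses the seed votes; that is wrong, because the first one does. A reader might also infer that the second model has almost no power; that is too general. With dev from the final EP, the only reference the article defines explicitly (in the sister model), and seeds leaning one way by 1-2 points, the joint test rejects in 67-100% of set A runs.

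What does not stand is that the first regression settles the matter. As printed it has one independent variable, and step 4 shows that it finds an association when no seed vote was ever displayed. Nor would a later choice of dev or coefficient put the seed votes into an equation that has already been printed without them.

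**Conclusion.** The point holds as a failure of identification, not as a general lack of power. The second model cannot separate seed influence from entry time, amount of feedback and type of respondent. It can miss real influence (about 5-11% rejection with dev from the display), and it can reject with no seeds shown if early entrants merely react more (about 38-100%, depending on assumptions). Where it does reject often under biased seeds, that rejection cannot be assigned to them. As printed, neither H0_2 analysis isolates the effect that H0_2 names.

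The algebra in steps 2 and 4 needs few assumptions. The percentages rest on assumed inputs and on a simple rule of one proportional revision, whereas participants may in fact re-rate as often as they like.

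A reader might go further and conclude that the primary result is compromised. The documents do not support that: H0_2 is a secondary hypothesis, and the primary comparison of the two lists is defined without it. What is affected is what may be said about whether seeding shaped the Real-Time list.

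**What to change.** Base H0_2 on the first regression, stated by outcome: final Real-Time mean rating on the seed-group mean rating, adjusted for participants' mean first (pre-feedback) rating of that outcome, with H0_2 tested on the seed coefficient. First ratings are pre-feedback by design, because the display appears only after an outcome is first rated.

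Keep the early/late model, reword its introduction as a descriptive association with entry time, define dev the same way throughout, and draw no conclusion about the seeds from it.

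A participant-level model using the gap between the displayed average with and without seed votes is another option, but it is less attractive. Its coefficient largely measures whether people follow feedback at all, and it has to drop the first raters, who are the most exposed to the seeds.

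The cost is a change of wording and some extra analysis. The seed votes are collected anyway, and first ratings are already needed to compute cor. Precision falls where seeds and panel agree closely. Outcomes added after launch have no pre-launch seed rating and would fall outside this regression.
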